## Background

Irritable bowel syndrome (IBS) is one of the most common functional gastrointestinal disorders in clinical practice. The diagnosis of IBS is based on symptoms defined by abdominal pain or discomfort associated with defecation or changes in bowel habits [1]. Recent pooled population-based meta-analysis indicated that the global prevalence of IBS was approximately 11.2% [2], and an early epidemiological study in Hong Kong showed that 13% of males and 21% of females in Hong Kong suffered from IBS [3]. To date, the treatment for IBS is unsatisfactory. Moreover, people with IBS frequently suffer from anxiety and depression, which can worsen the symptoms. Of those who do seek treatment, research has found that 54 to 94% have a psychiatric disorder such as an anxiety disorder or depression [4–6]. Up to the present, there has not been a satisfactory treatment of IBS in pharmacological approach nor complementary medicine [7]. In China, antibiotics, antispasmodics, and secretagogues are used to treat IBS, but the effectiveness varies [8]. Non-medication treatments such as dietary/nutritional and psychobehavioral therapy can be the alternatives; however, the requirement of high adherence may decrease the rates of treatment continuation [9, 10]. Acupuncture can be a more convenient option for patients with IBS as the treatment does not require daily intake of medication nor frequent clinical visits.

Acupuncture has been practiced empirically in China for several millennia, and it is increasingly accepted by practitioners and patients worldwide, especially during the last three decades [11, 12]. Currently, acupuncture treatment for IBS is a research hotspot in alternative medicine. A trial of acupuncture in 233 patients with IBS published in 2012 showed acupuncture improved their quality-adjusted life years [13]. Other reviews indicated that acupuncture was effective for IBS global symptoms [14, 15]. Research showed that electro-acupuncture had the same effectiveness as medication in decreasing diarrhea on IBS patients with additional improvement on the consistency of stool and visceral pain symptoms [16]. Besides, it is well demonstrated that acupuncture has broad therapeutic benefits in treating various psychiatric disorders. A recent meta-analysis indicated that acupuncture treatment was effective in alleviating various depressive symptoms [17].

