### Assignment and blinding

Simple, complete, non-sequential randomization numbers will be generated by the Random Allocation Software (Version 1.0.0), Isfahan, Iran, and kept by the principal investigator (PI). After the patient’s eligibility is confirmed, patients will be randomized to AC arm or SAC arm for 6 weeks. Only the acupuncturists are allowed to know the patients’ treatment. All other research members will be blind to the assignment. In addition, patients will also be blinded. They cannot visually detect sham or active acupuncture procedures.

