### Sample size calculation

According to a previous study, placebo is associated with high rates of resolution in a functional bowel disorder. Assuming that a difference of at least 30% between acupuncture and placebo is needed for a clinically important outcome, 51 patients per treatment group were deemed sufficient to achieve 80% power in detecting a treatment difference, based on a two-sided *χ*^2^ test without continuity correction at a significance level of 0.025 (used to maintain the overall significance level at 5%). Further assuming a 15% dropout rate, we concluded that we needed to recruit a total of 120 patients (60 per arm) for this trial to ensure statistically significant results. The calculation was performed using the StudySize 3.0 software (V. Frolunda, Sweden).

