### Statistical analysis

All efficacy and safety analyses will be conducted according to the intention-to-treat (ITT) principle. Missing values will be imputed by the last-observation-carried forward method. The statistical analysis will be performed using the Statistical Packages of Social Sciences (SPSS) for Windows version 25.0. The statistical significance is defined as a two-sided *P*-value of < 0.05. Baseline differences between the groups will be assessed with the use of Student’s *t*-test for normally distributed continuous variables and the non-parametric Mann-Whitney *U* test for non-normally distributed. For categorical variables, the chi-squared test or Fisher’s exact test will be used. Changes in IBS-SSS, HAMD-17, SDS, and IBS-QoL at each evaluation time point from baseline will be analyzed using the ANCOVA model, followed by the Bonferroni *t*-test to detect the differences between the two groups at each time point. Incidence of adverse events will be examined using the chi-square test.

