## Discussion and conclusion

The study is a single-blinded, randomized controlled clinical trial to evaluate the efficacy and safety of acupuncture for IBS, including all subtypes: IBS-C, IBS-D, IBS-M, and IBS-U. In addition to the change of bowel habits, people with IBS frequently suffered from anxiety, and depression or mood change further worsens the IBS. Currently, there is not any study on acupuncture in treating IBS digestive-psychological symptoms; therefore, the scalp points and abdominal points are included in this clinical trial. It would be the first of such research.

If the outcome from this study shows improvement in IBS, we may expect a larger scale of study. Research on the integration of non-medication treatments can be developed with the data from this clinical trial, such as electro-acupuncture with diet or lifestyle change, or integration of acupuncture and psychological cognitive-behavioral therapy.

The limitation of this study is that the selection of acupuncture points is standardized and utilized for every subject without syndrome differentiation. IBS can be differentiated into 4 subtypes, and each can be further sub-divided with Chinese medicine syndrome differentiation such as spleen dysfunction, liver depression, kidney Yang deficiency, and intestinal heat dampness. Although dysfunction of the spleen system is the leading cause of the problem, point selection according to each subtype may optimize the effectiveness of acupuncture. In addition, the environmental factors and dietary factors of the participants exposed to may affect the study result. We would require participants to record their daily diet on a diet diary, but no dietary modification would be given in our study.

In conclusion, this study will provide the basis for the effectiveness and safety of electro-acupuncture on IBS global treatment and would explore the possibility of acupuncture in the integrative treatment of psychological conditions.

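### Baseline significance tests cannot show whether a chance imbalance matters; describe baseline by arm and fix baseline IBS-SSS and HAMD-17 as covariates in the planned ANCOVA

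*Protocol article*

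**What the plan says.** Under Statistical analysis, the protocol article states: "Baseline differences between the groups will be assessed with the use of" Student's t-test, or the Mann-Whitney U test where the variable is not normally distributed. It continues: "For categorical variables, the chi-squared test or Fisher’s exact test will be used". The threshold comes from the same paragraph: "The statistical significance is defined as a two-sided" P-value below 0.05. The paragraph then plans an ANCOVA of the changes in IBS-SSS, HAMD-17, SDS and IBS-QoL, without naming covariates.

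Three other places bear on the point:

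- **Assignment and blinding:** "Simple, complete, non-sequential randomization numbers will be generated by the Random Allocation Software". Allocation is simple, and no stratification is stated.
- **Background and Discussion:** the protocol treats mood as a driver of symptoms. It says that "people with IBS frequently suffer from anxiety and depression, which can worsen the symptoms" and, later, that "depression or mood change further worsens the IBS".
- **Outcomes:** HAMD-17 is assessed as a difference from baseline, so its baseline value will be available.

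**The concern.** Arms formed by random allocation differ at baseline only by chance. A test of the hypothesis that chance alone produced the difference therefore answers a question that nobody is asking. What matters for the IBS-SSS comparison is the size of the imbalance and how strongly the variable predicts the outcome, and a P-value measures neither.

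Two misreadings follow easily. A non-significant result on a prognostic variable may be taken as evidence that the arms are comparable. A significant result on an unimportant variable may prompt an adjustment chosen after the data have been seen.

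This matters somewhat more here than in many trials. Simple allocation without stated stratification does nothing to balance depression scores, and the protocol itself says that depression worsens the condition under study. The variable that would deal with the problem is already being measured.

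**Working it through.** **Inputs from the protocol.** From Sample size calculation: "51 patients per treatment group were deemed sufficient to achieve 80% power in detecting a treatment difference" at a two-sided level of 0.025, and "we needed to recruit a total of 120 patients (60 per arm"). From Statistical analysis: two-sided 0.05. **Assumed, not in the protocol:** a partial correlation r of 0.2 to 0.3 between baseline HAMD-17 and the IBS-SSS outcome, given baseline IBS-SSS. SDs below are read on that adjusted scale.

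**1. The plan's own figure.** The control rate is not stated. With rates of 0.30 and 0.60 (pooled 0.45), the uncorrected chi-squared formula gives

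n = [2.2414·√(2·0.45·0.55) + 0.8416·√(0.30·0.70 + 0.60·0.40)]² / 0.30² = 50.96, so 51 per arm.

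Rates of 0.40 and 0.70 give the same. Then 51/(1 − 0.15) = 60 per arm, 120 in total. The plan's figures reproduce, and 60 per arm is used for baseline.

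**2. What the t-test can flag.** The standard error of a standardised baseline difference is √(2/60) = 0.183. The smallest significant difference is 1.980 × 0.1826 = 0.362 SD. This applies to continuous variables under a t-test with equal arms. With 51 per arm it is 0.39 SD, and with a 50:70 split 0.367 SD. It does not apply to categorical variables such as IBS subtype.

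**3. How often imbalance goes unflagged.** P(|difference| > 0.2 SD) = 2·[1 − Φ(0.2/0.1826)] = 0.27. The test flags 5%, so in about 0.27 − 0.05 = 22% of trials a given continuous variable differs by 0.2 to 0.36 SD without significance.

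**4. Typical size among non-significant results.** E(|Z| given |Z| < 1.96) = 2·[φ(0) − φ(1.96)]/0.95 = 2·(0.3989 − 0.0584)/0.95 = 0.717. Multiplied by 0.1826, this is 0.13 SD.

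**5. Effect on the IBS-SSS contrast if HAMD-17 is left out of the model.** Shift = r × imbalance. As a yardstick, the difference detectable with 51 per arm at 0.025 and 80% power is (2.2414 + 0.8416)·√(2/51) = 0.61 SD. This yardstick is derived here; the protocol sizes the trial on proportions.

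| Imbalance | r = 0.2 | r = 0.3 | Share of 0.61 SD |
|---|---|---|---|
| 0.13 SD (typical) | 0.026 SD | 0.039 SD | 4–6% |
| 0.36 SD (largest non-significant) | 0.07 SD | 0.11 SD | 12–18% |

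**6. Conditional error.** Take r = 0.3, nominal 5%. The critical value is 1.96 × 0.1826 = 0.358, and the standard error given the imbalance is 0.1826·√(1 − 0.09) = 0.174. For an imbalance of 0.35 SD the shift is 0.105, and the error is 1 − Φ((0.358 − 0.105)/0.174) + Φ((−0.358 − 0.105)/0.174) = about 7.7%. For 0.2 SD it is 5.2%. Averaged over all randomisations it remains 5%.

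**7. Gain from adjustment.** Residual variance is multiplied by 1 − r²: 0.96 for r = 0.2 and 0.91 for r = 0.3, a reduction of 4 to 9%.

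**8. Chance flags.** The number of baseline variables to be tested is not given. With 8 to 15 independent ones (assumed), the chance of at least one significant result is 1 − 0.95⁸ = 34% to 1 − 0.95¹⁵ = 54%. Correlated scales such as HAMD-17 and SDS would make the true figure differ.

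**The case against.** The strongest reply is that the tests decide nothing. The protocol says only that baseline differences will be assessed. It sets no pass or fail criterion, declares no arms comparable, and adds or drops no covariate on the strength of a P-value. Deleting the tests by itself would change no efficacy estimate. That stands.

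A reader might go further and infer that a depression imbalance would be cleared by a non-significant test and then left in the IBS-SSS comparison. The document does not support this. An ANCOVA is already planned, its covariates are not listed in the article, and such a list may properly sit in an analysis plan that is not shown. The missing list is not itself a fault.

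A reader might also take 0.36 SD as the usual distortion. It is the extreme. The typical non-significant imbalance is about 0.13 SD, the resulting shifts average zero over randomisations, and overall type I error is not inflated.

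Nor do the documents show that IBS subtype predicts IBS-SSS change. The Discussion's remark that points chosen by subtype might work better concerns the treatment effect, not prognosis. Finally, the Exclusion criteria remove patients with a history of mental illness or taking antidepressants. That may narrow the HAMD-17 range and weaken its correlation with the outcome.

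What the reply leaves standing is that the stated tests are uninformative, and that the model already planned can do the job they cannot.

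**Conclusion.** The point holds in a limited form. The protocol assesses baseline comparability with significance tests that cannot show whether an imbalance matters. The consequence is empty reassurance and an opening for post hoc adjustment; bias is not demonstrated. Under assumed partial correlations of 0.2 to 0.3, the shift in the IBS-SSS contrast is about 0.03 to 0.04 SD for a typical non-significant imbalance and 0.07 to 0.11 SD at worst, conditional on the imbalance observed. Neither the sample size nor the overall error rate is affected. The recommendation rests on simple allocation, the protocol's own statements about depression, and a baseline HAMD-17 that will be collected anyway. It is a nearly free improvement, not the repair of a broken analysis.

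**What to change.** In Statistical analysis, replace the baseline tests with a descriptive table by arm: mean and SD, or number and percentage, with standardised differences. State that the IBS-SSS ANCOVA includes baseline IBS-SSS and baseline HAMD-17 as fixed covariates whatever imbalance is observed, and that no covariate is added or dropped because of a baseline P-value. IBS subtype may be added as an option, but it should be fixed in advance if used.

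The cost is wording, one further degree of freedom for HAMD-17 (of about 120 − 3 = 117 in a model with arm and baseline IBS-SSS), up to three more for the four subtypes, and no new data. The expected return is a 4 to 9% reduction in residual variance under the assumed correlations, possibly less given the exclusions. The change should be made before unblinding.

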## Materials and methods

### Study design

This is a single-blinded randomized sham-controlled clinical trial with two arms. A total of 120 IBS patients will be recruited. The study will cooperate with Hong Kong Baptist University and University of Toronto. After a 2-week run-in period, eligible subjects will be randomly assigned to one of two arms, acupuncture (AC) arm and sham acupuncture (SAC) arm. Each eligible subject will go through a 2-week run-in-period, 6-week treatment period, and followed by a 6-week follow-up period. Five visits in total were scheduled for each subject in week 0, week 2, week 5, week 8, and week 14. The participant flowchart is listed in Fig. 1, and the participant timeline is listed in Fig. 2.

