### Inclusion criteria

Patients will be included if they have all the following at baseline and during the 2-week run-in period:
Fulfillment of the Rome IV criteria for IBSAge of 18 to 65 years (inclusive)IBS Symptom Severity Scale (IBS-SSS) (Appendix 1) > 75 points (a range of 0–500 points of VAS on five questions)

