### Outcomes

The primary outcome is the difference between baseline and 8 weeks and 14 weeks after randomization on IBS Symptom Severity Scale (IBS-SSS).

The secondary outcomes include (1) the difference between baseline and 8 weeks and 14 weeks after randomization on Hamilton Depression Rating Scale (HAMD-17), (2) the difference between baseline and 8 weeks and 14 weeks after randomization on Clinical Global Impression-Severity (CGI-S) and Self-Rating Depression Scale (SDS), and (3) the difference between baseline and 8 weeks and 14 weeks after randomization on IBS Quality of Life (IBS-QoL). IBS-SSS has been validated as a classical monitor of the disease since 1997 and has been widely adopted across IBS researches [30]. The specific assessment schedule is in Fig. 2. Safety profiles will be assessed by determining the important adverse events reported on in every treatment and follow-up interviews.

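### Two pre-randomisation IBS-SSS readings are implied, but the ANCOVA refers to one unspecified baseline; entering both readings may gain precision for one degree of freedom

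*Protocol article*

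**What the plan says.** **Eligibility.** The Inclusion criteria section opens: "Patients will be included if they have all the following at baseline and during the 2-week run-in period". One of the listed criteria is "IBS Symptom Severity Scale (IBS-SSS) (Appendix 1) > 75 points", on a scale of 0 to 500.

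**Timing.** Study design states: "Five visits in total were scheduled for each subject in week 0, week 2, week 5, week 8, and week 14". It also states: "After a 2-week run-in period, eligible subjects will be randomly assigned to one of two arms".

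**Outcome and model.** The Outcomes section defines the primary outcome as the IBS-SSS difference between baseline and weeks 8 and 14. Statistical analysis says that changes "at each evaluation time point from baseline will be analyzed using the ANCOVA model", followed by Bonferroni-adjusted comparisons of the arms at each time point. Neither section says which visit is baseline, whether baseline is one reading or an average, or which covariates enter the model. The visit-by-visit assessment schedule is in Fig. 2, which I could not read.

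**The concern.** The eligibility sentence treats baseline and the run-in as separate occasions on which the IBS-SSS threshold must be met. The outcome and the analysis then refer only to baseline. If that means one reading, the other is collected and has no stated use.

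IBS symptoms fluctuate, so one reading is a noisy measure of a patient's usual severity. A second reading taken before randomisation cannot be affected by treatment. Entering it as a covariate cannot bias the comparison and may reduce the residual variance of the primary analysis. What is at stake is precision, not validity.

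**Working it through.** **1. Are there two readings before randomisation?** The run-in (2 weeks), treatment (6 weeks) and follow-up (6 weeks) sum to 2 + 6 + 6 = 14, which is the last visit. Week 0 is therefore the start of the run-in and week 2 its end, when randomisation takes place. Outcomes counts weeks 8 and 14 from randomisation, which does not fit this 14-week total; I follow Study design. With IBS-SSS above 75 required on both occasions, readings at about weeks 0 and 2 are implied. This is an inference, because Fig. 2 was not readable.

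**2. The plan's own sample size.** Sample size calculation states that "51 patients per treatment group were deemed sufficient to achieve 80% power in detecting a treatment difference", for a 30% difference, a two-sided chi-square test without continuity correction, and alpha 0.025. No control rate is given. At 30% v 60%:

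n = [2.2414 × √(2 × 0.45 × 0.55) + 0.8416 × √(0.30 × 0.70 + 0.60 × 0.40)]² / 0.30² = (1.577 + 0.565)² / 0.09 ≈ 51 per arm.

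A control rate of 40% also gives 51; 25% or 45% gives 50, and 35% gives 52. Then 51 / 0.85 = 60 per arm, 120 in total. The figure reproduces. It is for a comparison of proportions with no covariate, so nothing below alters it.

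**3. Formulas for the covariate.** Take the outcome variance as 1. Let a be the correlation of week 0 with the outcome, b that of week 2 with the outcome, and c that between the two pre-randomisation readings.

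- One reading: residual variance 1 − a² or 1 − b².
- Both readings: 1 − (a² + b² − 2abc) / (1 − c²).
- If a = b = c = r, the second formula becomes 1 − 2r² / (1 + r).

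Modelling change or the follow-up value gives the same residual variance once the baseline used for the change is a covariate.

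**4. Equal correlations (assumed).**

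| r | one reading | both | reduction |
|---|---|---|---|
| 0.5 | 0.750 | 0.667 | 11.1% |
| 0.6 | 0.640 | 0.550 | 14.1% |
| 0.7 | 0.510 | 0.424 | 17.0% |

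**5. Unequal correlations (assumed).**

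| c | a (week 0) | b (week 2) | both | reduction v week 0 alone | reduction v week 2 alone |
|---|---|---|---|---|---|
| 0.7 | 0.50 | 0.50 | 0.706 | 5.9% | 5.9% |
| 0.8 | 0.50 | 0.50 | 0.722 | 3.7% | 3.7% |
| 0.7 | 0.45 | 0.50 | 0.730 | 8.4% | 2.6% |
| 0.8 | 0.40 | 0.50 | 0.750 | 10.7% | 0.0% |
| 0.7 | 0.45 | 0.55 | 0.689 | 13.6% | 1.2% |
| 0.8 | 0.40 | 0.55 | 0.693 | 17.5% | 0.6% |

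Example, fifth row: (0.2025 + 0.3025 − 2 × 0.45 × 0.55 × 0.7) / (1 − 0.49) = 0.1585 / 0.51 = 0.311, leaving 0.689. Against week 0 alone, 0.689 / 0.7975 = 0.864. Against week 2 alone, 0.689 / 0.6975 = 0.988.

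**6. Cost.** With all 120 analysed, residual degrees of freedom go from 120 − 3 = 117 to 116. The price is roughly 1/116, or about 0.9% of variance, so the net effect at the bottom of the range is close to nil.

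**The case against.** The strongest reply is that the article never says a reading is thrown away. It names no covariate at all, and covariate lists and the derivation of baseline are commonly left by an article to the full protocol or analysis plan. That is right. A reader might infer that the plan discards the run-in reading; the text supports only that it gives that reading no stated role.

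Second, the gain is not guaranteed. Equal correlations mean that readings two weeks apart agree no better than readings separated by the treatment or follow-up period, which is favourable to the proposal. If the later reading is already the baseline and is the more predictive, the gain can be close to zero. This also stands, and it is why the range starts at zero.

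Third, a reader might infer that the trial has no power to spare and that the second reading would lift it from 80% to about 85–87%. The documents do not support that. The 80% belongs to a chi-square test on proportions. No SD or mean difference for IBS-SSS is given, so the power of the ANCOVA is unknown. The 85–87% follows only if one supposes an effect that a single-baseline ANCOVA would detect with exactly 80% power, under equal correlations of 0.5–0.7.

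Fourth, single-baseline ANCOVA is standard, valid and unbiased. That stands too. What remains is that two readings are implied, the stated analysis refers to one, and using both is legitimate and nearly free.

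**Conclusion.** The point holds as an efficiency recommendation. It is not an error in a stated figure, a bias or a contradiction. On assumed correlations, the second reading cuts the residual variance of the IBS-SSS comparison by:

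- about 0–4% where it adds little to the reading already used;
- about 6% if the two readings correlate 0.7 with each other and 0.5 with the outcome;
- 11–17% if all correlations are equal at 0.5–0.7;
- 13.6% or 17.5% in the two cases where week 0 alone would be used and week 2 is clearly the more predictive (0.55 against 0.45 or 0.40).

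All of this rests on IBS-SSS being recorded at both week 0 and week 2 with the latter taken before randomisation, and on correlations that the documents do not give. Whether precision is in fact lost cannot be settled from the article, since the full analysis specification may already use both readings.

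There is a further small benefit. With both readings in the model, the estimated treatment effect is the same whichever visit is called baseline for the change score, so that undefined choice no longer affects the primary comparison.

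**What to change.** In Statistical analysis, state that the ANCOVA for IBS-SSS at weeks 8 and 14 enters both pre-randomisation IBS-SSS readings, week 0 and week 2, as separate covariates, and name the visit that serves as baseline for the change score. Confirm against Fig. 2 that both readings are scheduled and that the week 2 reading precedes randomisation.

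Extend this to HAMD-17, SDS and IBS-QoL only if the schedule shows two pre-randomisation readings for them; the eligibility criteria imply a second reading for IBS-SSS alone.

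The cost is one sentence and one degree of freedom. It needs no new visits, data or patients, and the planned 51 and 60 per arm and the stated 80% power are unchanged. The sentence should be fixed before any unblinded data are seen.
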